##### Dietary intake at baseline and after 16 weeks

Dietary intake of energy and protein will be assessed by means of a 24-h recall interview. A checklist of specific foods and beverages will be used to verify the reported intake.

Data from the 24-h recall interview will be entered in a dietary program (VITAKOST; https://www.vitakost.dk/da/hjem) that uses data from the national food database. Standard portion sizes from the publication “Dimensions, weight and portion sizes of foods” [31] will be used if insufficient detail is given by the participants. The cutoff for underreporting of energy will be based on an estimated minimum of energy expenditure [8]. The average intake of energy and protein for each participant will be reported and compared with the recommended intake for this population (see below). The results will be presented as a percentage of the requirement.

##### Energy and protein requirements at baseline and after 16 weeks

Energy and protein requirements will be estimated on the basis of a calculation of the basal metabolic rate using the Oxford equations for, respectively, women and men 61–70 and 70+ years of age. To include physical activity, an activity factor of 1.4 is used. Protein requirement is estimated as 1.2 g/kg body wt as recommended for older adults 65+ years of age [20]. The average requirement for each participant will be reported and compared with the dietary intake (see above).

##### Nutritional status at baseline and after 16 weeks

Nutritional status will be assessed by means of weight, which is measured on a calibrated scale with patients wearing light indoor clothes and no shoes. To take the weight of clothes into account, 0.5 kg will be removed from the measured weight. Self-reported information about weight will also be obtained by the research dietitians during the contact with the intervention group. Measurement of height is often not feasible in this old and frail population with chronic disease, because some lack the ability to stand independently. Data on height will be retrieved from self-reported height and only collected at baseline. Body mass index is calculated as actual weight in kilograms divided by the square of height in meters. The average change in kilograms and percentage will be reported for each group.

##### Mortality after 30 days, 112 days, and 6 months

Mortality will be assessed using data from the hospital patient register during the intervention and within 6 months. The prevalence in each group will be calculated.

##### Evaluation of the intervention

As part of the two phone contacts performed by the research dietitians, taste experience of the goodie bag and food package and the experience of the transition between sectors will be assessed. This will be done by means of a questionnaire asking about the appearance and taste of the food and about the experience of the transfer (rated on a scale from 1 to 5, with 5 being best).

### Data and statistical analysis

The full analysis set will follow the intention-to-treat principle and will include all randomized patients for whom a baseline assessment is conducted, regardless of later temporary or permanent loss to follow-up. Lack of outcome data due to loss to follow-up or if data were unobtainable (i.e., if a patient was readmitted to the hospital and did not want to participate any further) will be treated as missing data and will be excluded from the final analysis. Subgroup comparisons will be made between fully compliant participants (i.e., those who, respectively, do and do not achieve an intake of energy and protein at or above 75% of their estimated requirement).

Descriptive and summary statistics will be used to quantify participants’ characteristics and outcome variables. Nonparametric statistics will be applied whenever nonnormality of the outcomes is detected. Unpaired data will be analyzed by Student’s *t* test or the Mann-Whitney *U* test, and paired data will be analyzed by a paired Student’s *t* test or Wilcoxon signed-rank test as appropriate. For dichotomous variables, difference in proportions will be analyzed by a chi-square test. To detect correlations, Pearson’s or Spearman’s correlation will be used as appropriate. For comparison of tests within the group, general linear models will be used. Two-sided tests of statistical significance will be used in statistical analysis. A *p* value < 0.05 will be considered statistically significant. All analyses will be performed using SAS Enterprise guide 7.1 (SAS Institute, Cary, NC, USA).

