#### Sample size

Power calculations are made relative to the primary endpoint, which is the number of admissions after 6 months. A previous study focusing on a systematic nutritional effort in connection with discharge showed a reduction in the number of admissions (28% in the intervention group and 52% in the control group) during the first 6 months after discharge [2]. By accumulating these numbers with a significance level of 0.05% and a power of 0.80, there must be 64 older patients in each group, a total of 128, to ensure enough power to assess the older medical population. To investigate if patients with cancer also could benefit from the intervention, it is further desired to add a total of 40 extra patients with a cancer diagnosis. However, because it is expected that patients with cancer will be readmitted often, we want to be able to remove these patients from the analyses and still have sufficient power to assess the effect on older medical patients. To also account for dropouts, the goal is 100 patients in each group, for a total of 200 participants.

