#### Primary outcome

##### Admissions after 6 months

Nonplanned admissions within 6 months will be assessed using data from the hospital patient register, where the number of admissions can be found. The prevalence in each group will be calculated. The length of stay at each admission is also recorded and averaged for the two groups.

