#### Secondary outcomes

##### Readmissions

Readmissions, defined as admission within 30 days postdischarge, will be assessed by data from the hospital patient register, where the number can be found. The prevalence in each group will be calculated. The length of stay at each readmission is also recorded and averaged for the two groups.

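### The missing-data exclusion does not exempt the register endpoints, so as worded it can remove randomised patients whose primary event is already known

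*Protocol article*

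**What the plan says.** All places are in the protocol article.

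- **Data and statistical analysis, analysis set.** The full analysis set follows intention to treat and "will include all randomized patients for whom a baseline assessment is conducted, regardless of later temporary or permanent loss to follow-up".
- **Data and statistical analysis, next sentence.** Outcome data that are lacking through loss to follow-up, or that cannot be obtained, are left out of the final analysis. One case is given, introduced by i.e.: a patient who "was readmitted to the hospital and did not want to participate any further) will be treated as missing data and will be excluded". The sentence names no outcome to which it does or does not apply.
- **Admissions after 6 months (primary outcome).** "Nonplanned admissions within 6 months will be assessed using data from the hospital patient register, where the number of admissions can be found".
- **Readmissions (secondary outcome).** "Readmissions, defined as admission within 30 days postdischarge", again from the register. Admissions to day 112 and mortality have the same source.
- **Sample size.** The assumed risks are "28% in the intervention group and 52% in the control group) during the first 6 months after discharge". The target is raised to 100 per group, partly for dropouts, but no dropout rate is given.
- **Procedure.** Eligible patients who decline the trial are asked for permission to use their register data.
- **Strengths and limitations.** Register collection is offered as protection against bias in an unblinded trial.

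**The concern.** A patient who is readmitted without plan within 6 months has had the primary event. The rule's one example of missing data is a readmitted patient who then stops taking part. If the rule is applied to the admission endpoints, whether such a patient stays in the analysis depends partly on the outcome itself, and the events removed are already known.

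Two things are at stake. First, the observed admission risk falls in any arm where such patients are excluded. Second, if the share excluded differs between arms, the comparison is biased. The trial is unblinded, and Table 1 schedules telephone contacts for the intervention group only, so equal withdrawal cannot be taken for granted. The loss would also be avoidable, because register endpoints need no further contact with the participant.

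**Working it through.** **Inputs.** Risks of 52% (control) and 28% (intervention), power 0.80 and 100 per group come from Sample size. The two-sided test and the chi-square test for proportions come from Data and statistical analysis. The share *w* of patients with an event who withdraw and are excluded is in no document. It is assumed here, from 0% to 30%.

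**1. The plan's own figure.** The pooled normal formula, two-sided alpha 0.05, is

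n = [1.96·√(2·0.40·0.60) + 0.8416·√(0.52·0.48 + 0.28·0.72)]² / 0.24² = (1.358 + 0.565)² / 0.0576 = 64.2, so 65 per group.

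The arcsine version gives 63.9, so 64. The stated 64 is reproduced. The printed significance level of 0.05%, read literally as 0.0005, would need 154 per group, so 0.05 is used here.

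**2. Effect of the exclusion.** With true risk p and n per arm:

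- patients left = n(1 − pw)
- observed risk = p(1 − w) / (1 − pw)
- power = Φ[(difference − 1.96·SE₀) / SE₁], with SE₀ from the pooled risk and SE₁ from the separate risks, both on the reduced numbers.

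Example, w = 30% in control and 10% in intervention:

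- control: 0.52·0.7 / (1 − 0.156) = 0.364/0.844 = 43.1%, with 84.4 patients left
- intervention: 0.28·0.9 / (1 − 0.028) = 0.252/0.972 = 25.9%, with 97.2 left.

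Results at 100 per arm (differences taken before rounding):

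| w, control / intervention | Patients left | Observed risk | Difference, points | Power |
|---|---|---|---|---|
| 0% / 0% | 100 / 100 | 52.0% v 28.0% | 24.0 | 0.94 |
| 10% / 10% | 94.8 / 97.2 | 49.4% v 25.9% | 23.4 | 0.92 |
| 20% / 20% | 89.6 / 94.4 | 46.4% v 23.7% | 22.7 | 0.90 |
| 30% / 30% | 84.4 / 91.6 | 43.1% v 21.4% | 21.7 | 0.88 |
| 30% / 10% | 84.4 / 97.2 | 43.1% v 25.9% | 17.2 | 0.69 |
| 10% / 30% | 94.8 / 91.6 | 49.4% v 21.4% | 28.0 | 0.98 |

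The higher power in the last row is not a gain. It comes from an overstated effect.

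**3. No true effect.** With a risk of 40% in both arms and w = 30% in control, 10% in intervention:

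- control: 0.28/0.88 = 31.8%
- intervention: 0.36/0.96 = 37.5%.

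This is a spurious 5.7 points against the intervention; the reverse split gives 5.7 points in its favour. The two-sided rejection rate at nominal 0.05 is about 0.13. At a common risk of 28% it is 0.11, and at 52% it is 0.13.

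**The case against.** The strongest reply is that the sentence concerns missing data, not patients. Read outcome by outcome, a participant who refuses the day-112 visit lacks quality of life, appetite, chair stand, diet and weight, but not a register count. The rest of the article fits that reading: it relies on the register to limit bias and seeks register data even from those who decline. On the same view, the first sentence sets who belongs to the analysis set and the second says how missing values are treated, so the two need not collide.

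This is a fair reading, and it may be what the sponsor intends. It does not remove the point. The sentence refers to outcome data and the final analysis without limit, nothing says that register follow-up continues after a participant stops, and its one example is a readmitted patient. The dropout allowance is added to a sample size built on the register endpoint, which suggests that dropouts may be expected to be lost from it.

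Other parts of the reply stand and limit the claim:

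- A reader might infer that readmission alone removes a patient, so that the 16-week measures would describe only those never readmitted. The text requires both readmission and refusal to continue.
- A reader might infer that admission risk is bound to be underestimated in both arms. That holds only if the rule is applied to register endpoints and patients with events do withdraw in both arms.
- A reader might infer that more withdrawal in the control group is likely. More contact could retain intervention patients or give them more occasions to refuse, and the documents do not settle which.
- Not every readmission is a primary event; it must be nonplanned.
- Applying *w* to all 6-month events leans towards the pessimistic side, because a first admission after day 112 cannot cause refusal of the day-112 visit.

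**Conclusion.** The point holds as a defect in a stated rule. The exclusion is not confined to outcomes that depend on the participant, and following it as worded can discard known primary events despite the intention-to-treat commitment just before it. The documents do not show that patients will in fact be dropped from the primary analysis; that depends on how the sentence is applied.

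The size rests wholly on assumed withdrawal shares. If withdrawal after an event is modest and equal, the harm is small: at 10% in both arms the difference moves from 24.0 to 23.4 points. The serious case is unequal withdrawal, where 30% against 10% shifts the estimated difference to about 17 or 28 points depending on which arm loses more, and more than doubles the type I error at a 40% risk. The direction cannot be known beforehand, which is a reason to settle the rule before the analysis.

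**What to change.** Reword the missing-data sentence along these lines:

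- Exclusion for missing data applies only to outcomes that need the participant, namely home-visit and questionnaire measures.
- Nonplanned admissions, readmissions, length of stay and mortality are analysed from the register for every randomised patient in the allocated group, including those who end study contact, unless consent to the use of register data is withdrawn.
- Admissions recorded before withdrawal count as events where consent allows.
- A sensitivity analysis covers patients whose register data cannot be used.

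For each withdrawal, record whether it ends study contact only or also the use of register data. The phrase in the current example does not tell these apart.

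The method for missing 16-week outcomes, such as multiple imputation, is a separate choice and can be left to the SAP.

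The cost is a few sentences and one added analysis. The register is already the planned source, so no new data source is needed.

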### Outcome assessments

The intervention will last 16 weeks (see Table 1). Assessments of the participants will be conducted by the research dietitian at baseline before randomization. After 16 weeks, data are collected by a research assistant who is not a part of the intervention. In addition, information will be collected from the hospital patient register at baseline and after 4, 30, and 112 days (Fig. 1 shows the SPIRIT figure). Data are collected using specific forms on paper created by the investigators. The researchers will meet regularly to monitor the trial process and check, for example, to see how recruitment is progressing and whether all outcome data are collected according to the protocol to ensure data quality.

Primary and secondary outcomes are described in detail below.

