##### Quality of life at baseline and after 16 weeks

Health-related quality of life will be assessed using the EuroQol–5 dimensions–3 levels (EQ-5D-3L). The EQ-5D-3L questionnaire comprises five domains: mobility, self-care, usual activities, pain/discomfort, and anxiety/depression. Each domain has three levels, ranging from no problems to extreme problems. The raw score must be converted to an EQ-5D-3L score. In addition, the participant is asked to record his/her self-rated health on a vertical visual analogue scale where the endpoints are labeled “Best imaginable health state” and “Worst imaginable health state” [26]. Permission to use the questionnaire has been obtained from the EuroQol Research Foundation.

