##### Appetite at baseline and after 16 weeks

Appetite will be assessed using the SNAQ. The SNAQ consists of four questions about appetite, taste, satiety, and number of meals. Each question has five possible answers, and the participants are asked to choose the category that reflects their situation. The questionnaire results in a score ranging from 5 to 20. A score ≤ 14 is predictive of 5–10% weight loss [30]. The score for each participant will be recorded at the two time points.

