##### Physical performance status at baseline and after 16 weeks

Physical performance status will be assessed by means of the 30-s chair stand. The participants are asked to fold their arms across their chest and to stand up and sit down on a chair without pushing off with their arms as many times as possible for 30 s. The arms may be used for assistance or for safety if needed [10]. The mode of chair stand will be registered, and the number of chair stands for each participant will be recorded at the two time points. An improvement in physical performance will be considered present if a participant no longer needs the arms when doing the test.

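### The continuous 16-week secondary outcomes are planned for unadjusted two-sample tests although their pre-randomization values are collected; a baseline-adjusted comparison between arms would be more precise at no cost in data

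*Protocol article*

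**What the plan says.** The protocol article's section on data and statistical analysis lists tests by type of data and does not assign them to outcomes.

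- Between groups: "Unpaired data will be analyzed by Student’s *t* test or the Mann-Whitney *U* test".
- Paired observations: "paired data will be analyzed by a paired Student’s *t* test or Wilcoxon signed-rank test as appropriate".
- The only regression model: "For comparison of tests within the group, general linear models will be used".
- Choice between the two families of tests: "Nonparametric statistics will be applied whenever nonnormality of the outcomes is detected".

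The outcome sections show that a baseline value exists for each continuous 16-week outcome. The headings include "Quality of life at baseline and after 16 weeks" and "Physical performance status at baseline and after 16 weeks", and for appetite the text says "The score for each participant will be recorded at the two time points". Dietary intake and weight follow the same two-visit pattern, and weight is to be summarized as change in kilograms and in percent. On timing, the section on outcome assessments states: "Assessments of the participants will be conducted by the research dietitian at baseline before randomization". These values therefore cannot be influenced by allocation and are proper covariates.

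**The concern.** Two things are at stake, both limited to the continuous secondary outcomes.

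The first is precision. A two-sample test that ignores the baseline leaves variation between patients in the error term that the trial has already measured. The sample size was set for admissions alone, so nothing was planned to secure power for quality of life, function or intake. Missing 16-week outcomes are to be excluded, so fewer than 100 per arm are likely to contribute.

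The second is interpretation. Baseline is taken in hospital, in patients selected for nutritional need and already on an enriched menu with dietitian follow-up. Week 16 is a home visit. Both arms can be expected to change through recovery and regression to the mean, whatever the allocation. Paired tests within each arm, together with a linear model reserved for comparison within the group, leave room for reading a change that is significant in one arm only as a treatment effect.

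**Working it through.** **The plan's own figure.** The only sample size is for admissions within 6 months: 28% against 52%, power 0.80, 64 per group. Taking the significance level as 0.05 two-sided, with pooled proportion 0.40:

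n = [1.96·√(2·0.40·0.60) + 0.8416·√(0.28·0.72 + 0.52·0.48)]² / 0.24² = (1.358 + 0.565)² / 0.0576 ≈ 64.2, so 65 per group. The arcsine formula gives 63.9, so 64.

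The figure reproduces. It concerns a binary outcome with no baseline value, so this point does not touch it.

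**Inputs for the continuous outcomes.** From the article: 1:1 allocation, target 100 per arm, two-sided testing at 0.05. Assumed: r between baseline and week 16 of 0.3 to 0.7, because the article gives none. The formulas are large-sample. The change-score formula also assumes equal standard deviations at the two visits.

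**Formulas.** The variance of the between-arm difference, relative to a week-16-only comparison, is:

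- analysis of covariance (ANCOVA): 1 − r²
- change score: 2(1 − r)
- hence ANCOVA relative to change score: (1 − r²) / [2(1 − r)] = (1 + r)/2

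With 100 per arm and 80% power, the detectable difference without adjustment is (1.96 + 0.8416)·√(2/100) = 0.396 SD. With adjustment it is 0.396·√(1 − r²). For an effect that the unadjusted test detects with 80% power, adjusted power is Φ(2.8016/√(1 − r²) − 1.96).

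| Assumed r | 0.3 | 0.5 | 0.7 |
|---|---|---|---|
| ANCOVA variance against week 16 only | 0.91 | 0.75 | 0.51 |
| Extra patients the unadjusted test needs, 1/(1 − r²) − 1 | 10% | 33% | 96% |
| Patients per arm with ANCOVA matching 100 unadjusted | 91 | 75 | 51 |
| Power where unadjusted has 80% | 84% | 90% | 97.5% |
| Detectable difference, SD (unadjusted 0.396) | 0.378 | 0.343 | 0.283 |
| Change-score variance against week 16 only | 1.4 | 1.0 | 0.6 |
| ANCOVA variance against change score | 0.65 | 0.75 | 0.85 |

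Outside this range the gain can be small. At r = 0.2 it is 1/0.96 − 1, about 4% more patients. At r = 0.9, ANCOVA variance is (1 + 0.9)/2 = 0.95 of that of a change score. These figures apply to comparisons of means; no equivalent was worked out for the Mann-Whitney test.

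**Within-arm tests.** Suppose both arms truly change by the same amount and each paired test has power p. Exactly one arm is then significant with probability 2p(1 − p): 0.42 at p = 0.3, 0.50 at p = 0.5 and 0.32 at p = 0.8. A direct between-arm test would be significant with probability 0.05.

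**The case against.** The strongest reply is that nothing here is wrong in the strict sense. An unadjusted two-sample test is unbiased under randomization, and its standard error already allows for chance imbalance at baseline. A reader might infer that the planned comparisons are invalid; the document does not support that. This part of the reply stands, and the point is one of efficiency.

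Next, the text is a list of tests by data type. It does not say whether week-16 values or changes enter the two-sample test, and the weight section points to changes. It does not say that paired data means testing before against after within each arm; comparing each participant's intake with that participant's requirement is also paired. The sentence on general linear models is unclear. All of this is fair, but it does not remove the point: in large samples ANCOVA is at least as precise under either reading, and no baseline-adjusted comparison between arms is named.

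A reader might also infer that the investigators will claim effects from within-arm p values. The article does not say so, and it does provide between-group tests. The misreading is a risk left open, not a stated plan.

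The size is uncertain too. A single 24-hour recall, taken once in hospital and once at home, may correlate weakly, so the gain for intake may be slight. For weight, r may be high, and then little is gained over change scores. A gain of 33% to 96% across all outcomes cannot be claimed.

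Finally, covariates for secondary outcomes are often left to the analysis plan, which is not at hand. Here, however, the article names the methods and places the linear model on the within-group side, so this is a stated choice that can be improved.

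**Conclusion.** The point holds as a recommended improvement for the continuous secondary outcomes measured at both visits: EQ-5D and its visual analogue scale, SNAQ, chair stands, energy and protein intake, and weight. The named tests are valid but less precise than a baseline-adjusted comparison. For an assumed r of 0.3 to 0.7, adjusted variance is 0.91 to 0.51 of a week-16-only comparison and 0.65 to 0.85 of a change-score comparison. Where each outcome falls cannot be told from the article.

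It would be too strong to say that power is lost for the outcomes the trial chiefly aims at. The aim singles out admissions and readmissions. These and mortality have no corresponding baseline value, so they and the sample size are unaffected.

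**What to change.** For each continuous 16-week outcome, name one between-arm analysis: a linear model of the week-16 value on arm and baseline value, reporting the adjusted difference and its 95% confidence interval. If residuals are skewed, use robust or bootstrap standard errors, so that the quantity estimated does not switch between means and ranks after a normality check. Cancer status may be added as an optional covariate; the point does not depend on it.

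Report within-arm changes descriptively, without p values, and say that conclusions about the intervention rest on the between-arm difference. Reword the sentence on general linear models to match.

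The cost is wording in the analysis plan, fixed before the between-arm comparisons are run. The data are already scheduled, and the named SAS software fits such models. The change does not address the exclusion of patients with missing 16-week outcomes.
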